### Adverse events management

Complications include but are not limited to: suspected medication or allergic reaction, suspected myocardial infarction, stroke, deep vein thrombosis, pulmonary embolism, and renal failure. Other side effects that have been reported have been minor including headache, upset stomach, flushing, and hypotension. To date there has been no clear association between the use of anti-fibrinolytics, such as TXA and EACA, and renal failure or thrombosis [7,8]. A similar medication with anti-fibrinolytic properties, aprotinin, did lose FDA approval over concerns regarding renal failure in cardiac patients and the theoretical risk of thrombosis [9]. Aprotinin functions as a serine protease inhibitor. In contrast, TXA and EACA are synthetic lysine analogs that bind to and produce a structural change in plasminogen preventing conversion of plasminogen to plasmin and conversion of fibrinogen to fibrin. TXA and EACA therefore have a dual mechanism of anticoagulation: decreased fibrinolysis and decreased platelet aggregation due to the inactivation of plasmin. This difference in mechanism most likely accounts for the lack of association between the use of anti-fibrinolytics and renal failure [7,8]. Regardless, patients in the study are carefully monitored for signs of renal failure post-operatively. Any patient with an elevated or rising creatinine is carefully followed by resident and attending orthopaedic surgeons, internal medicine physicians, and the research fellows. If the elevation in creatinine is suspicious for renal failure, patients will be "unblinded" and treated appropriately. TXA and EACA have been used most in cardiac and spinal surgery and meta-analysis has clearly shown a reduction of intra-operative blood loss and allogenic transfusion rate with these medications [6-8,10,11,13].

Considering the reported reduction in operative blood loss and allogenic transfusion rate in both the cardiac and spine literature, the benefits of treatment outweigh the potential side effects. While these medications are widely used, they are currently not the standard of care in spinal surgery. This study aims to delineate the benefits of TXA versus EACA in spinal surgery, which may help to identify the patients most in need of this treatment. Complications will be diligently recorded and reported in the final manuscript.

### Ethics, informed consent, and safety

The Institutional Review Board (IRB) of NYU approved the research protocol. If the patient wishes to enroll in the study, the IRB approved informed consent process is undertaken. A copy of the signed informed consent is issued to the family during the pre-operative office visit. The consent form includes the purpose of the study, a description of the study, costs and reimbursements, potential risks and discomforts as well as the primary investigators' contact information. If the patient is a minor, consent is obtained from the guardian of the minors using an NYU IRB approved consent form. Consent is also obtained from minors using an NYU IRB approved consent form.

Consented individuals are informed of the use of anti-fibrinolytic medication to control intra-operative and postoperative bleeding. The risks, benefits, advantages, and disadvantages of the use of TXA versus EACA versus placebo to control blood loss are detailed with the patient and family, as part of their routine pre-operative visit with their surgeon. The patient and family are diligently informed that while TXA and EACA have individually been shown to reduce total blood loss, neither medication is recognized as the standard of care. The relative affect of these medications with relation to transfusion rate and patient outcomes is also not fully known.

### Patient selection

The study concerns patients undergoing thoracic and/or lumbar spinal surgery for the correction of adolescent, idiopathic scoliosis (AIS), neuromuscular scoliosis (NMS), and adult deformity (AD). Inclusion and Exclusion criteria are included in Table 1.

**Table 1 T1:** Inclusion and Exclusion Criteria

All Participants	
Inclusion	Exclusion
1. Undergoing thoracic and/or lumbar surgery for correction of condition via posterior spinal fusion of greater than 6 levels	1. No renal dysfunction identified by elevated blood urea nitrogen (BUN) and creatinine (CR) or BUN to CR ratio greater than 20:1
	2. Hold religious and/or other beliefs limiting blood transfusion
	3. Currently use anti-coagulant medication or have past medical history leading to abnormal coagulation profile pre-operatively
	4. Significant past medical history preventing the use of TXA or EACA described in the protocol
**AIS**	
Inclusion	Exclusion
1. Between 10 and 21 years of age	1. Previous corrective spinal surgery that is being revised
2. BMI between 5th and 95th percentiles	
**AD**	
Inclusion	Exclusion
1. Between 18 and 80 years of age	1. Any history of coronary artery disease with stent placement
**NMS**	
Inclusion	Exclusion
1. Between 10 and 80 years of age	1. Congenital and syndromic scoliosis
	2. Previous corrective spinal surgery that is being revised

The maximum total number of patients enrolled will be 150 of AIS (50 in each treatment arm), 90 for NMS (30 in each treatment arm), 150 for AD (50 in each treatment arm). These numbers were estimated by critically reviewing the existing spine and cardiac literature comparing TXA and EACA against placebo [6-20]. A power analysis was conducted using the literature to determine the number of patients necessary to attain significant results (Tables 2 and 3).

**Table 2 T2:** Power study to determine number of patients needed in AIS group.

	TXA		Amicar		Control		
	**Blood loss**	**Standard Deviation**	**Blood Loss**	**Standard Deviation**	**Blood Loss**	**Standard Deviation**	**Sample Size Needed**

Intra-op blood loss	1072 mL	+/- 425 mL	-	-	1420 mL	+/- 644 mL	58

Intra-op blood loss	1072 mL	+/- 425 mL	893 mL	+/- 220 mL	-	-	80

Total blood transfused	1253 mL	+/- 884 mL	-	-	1784 mL	+/- 733 mL	55

Total units transferred	-	-	1.2 U	+/- 1.1 U	2.2 U	+/- 1.3 U	34

**Table 3 T3:** Power study to determine number of patients needed for NMS group

	TXA		Amicar		Control		
	**Blood loss**	**Standard Deviation**	**Blood Loss**	**Standard Deviation**	**Blood Loss**	**Standard Deviation**	**Sample Size Needed**

Intra-op blood loss	1408 mL	+/- 605 mL	-	-	2690 mL	+/- 1266 mL	14

Intra-op blood loss	1976 mL	+/- 860 mL	1117 mL	+/- 718 mL	-	-	30

Total blood transfused	808 mL	+/- 531 mL	-	-	1391 mL	+/- 723 mL	34

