**Discussion:**

The primary goal of the study is to determine perioperative blood loss as a measure of the efficacy of TXA, EACA, and placebo. Based on current literature and the mechanism by which the medications act, we hypothesize that TXA will be more effective at reducing blood loss than EACA or placebo and result in improved patient outcomes.

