### Statistical considerations

While useful, this analysis is limited by the great variability in study design and control groups between prior orthopedic studies. Since no orthopedic study has compared TXA and EACA together, conducting a power analysis required pooling of data from two or three studies. This proved difficult, as control groups were dissimilar between the studies (Table 2).

Power analysis was performed multiple times using data from several studies. When estimating the sample size required comparing TXA and EACA, attempts were made to choose two studies with similar intra-operative blood losses within the control groups. A cardiac study, albeit with dissimilar sample variance, was also used to estimate the sample size needed for this study. Finally, determining the sample size for outcomes of total blood loss and transfusion requirements proved difficult as even fewer studies reported these outcomes. Blood loss will be estimated in the operation room, but will also be calculated taking into account patient body mass, pre/postoperative hematocrit, and relative fluid balance [21-23]. This will minimize the variance in reported blood loss. A power analysis will be performed again once 60 patients with AIS, NMS, or AD have been enrolled into the study.

With a single institution of surgeons and anesthesiologists participating in the study, we expect a smaller variation in operative blood loss than reported in prior studies. Data will not only be analyzed for all patients collectively, but will also be stratified by diagnosis (AIS, NMS, and AD). The purpose of stratifying into these groups is threefold. First, separation by diagnosis allows for more diligent control of patient-related factors that may affect blood loss and transfusion rate. Secondarily, stratification by diagnosis allows for a better understanding of which patients benefit most from one treatment option over another. Lastly, it allows for a broader application of the results from this study not only to patients with AIS, but to all spinal deformity patients.

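### The AIS arm size of 50 is below three of the four AIS figures in the power table, the seven table rows do not share one alpha and power, and AIS TXA versus EACA falls short of 80% power at two-sided 0.05 or stricter

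*Protocol article*

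**What the plan says.** Under Patient selection, the text below Table 1 sets the maximum enrollment as "150 of AIS (50 in each treatment arm), 90 for NMS (30 in each treatment arm), 150 for AD (50 in each treatment arm". It attributes these numbers to a review of the spine and cardiac literature and then says: "A power analysis was conducted using the literature to determine the number of patients necessary to attain significant results (Tables 2 and 3".

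Table 2 is captioned "Power study to determine number of patients needed in AIS group" and Table 3 "Power study to determine number of patients needed for NMS group". Neither table has an AD row. Neither the tables nor the text gives alpha, power, sidedness, or whether the sample size is per arm or in total. The two AIS blood-loss rows read "Intra-op blood loss 1072 mL +/- 425 mL - - 1420 mL +/- 644 mL 58" (TXA against control) and "Intra-op blood loss 1072 mL +/- 425 mL 893 mL +/- 220 mL - - 80" (TXA against EACA).

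The Discussion part of the Abstract states the direction expected: "we hypothesize that TXA will be more effective at reducing blood loss than EACA or placebo and result in improved patient outcomes". Statistical considerations concedes that the TXA-EACA inputs came from different studies with dissimilar control groups, and adds: "A power analysis will be performed again once 60 patients with AIS, NMS, or AD have been enrolled into the study".

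**The concern.** The tables are offered as the basis for the arm sizes, yet the AIS arm of 50 is smaller than three of the four AIS figures (58, 80, 55). The largest, 80, belongs to the head-to-head comparison of TXA with EACA, which is the gap in the literature that the trial sets out to fill. A reader cannot tell what power the AIS comparison has, or whether the table figures are right.

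The protocol's own Discussion criticizes the earlier cardiac trials for being badly powered for TXA against EACA. If the AIS comparison has the same weakness, the protocol should say so. AIS, NMS and AD are each to be analyzed separately, so the arm size within a diagnosis matters and not only the pooled total.

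**Working it through.** **Inputs.** Means and SDs are from Tables 2 and 3; arm sizes are from Patient selection. Alpha, power and unit are not stated, so they are inferred or varied below.

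**Step 1: reproduce the tables.** For two means with unequal SDs and 1:1 allocation,

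n per arm = (z₁₋α/₂ + z₁₋β)² × (s₁² + s₂²) / d².

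At two-sided 0.01 and 80% power the first factor is (2.576 + 0.842)² = 11.68. AIS TXA-control: 425² + 644² = 595,361; d² = 348² = 121,104; n = 11.68 × 4.916 = 57.4, rounded up to 58 as stated. All rows:

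| Row | d | s₁² + s₂² | Stated | 0.01, 80% | 0.0167, 85% | 0.05, 80% |
|---|---|---|---|---|---|---|
| AIS TXA-control, blood loss | 348 | 595,361 | 58 | 57.4 → 58 | 57.8 | 38.6 → 39 |
| AIS TXA-EACA, blood loss | 179 | 229,025 | 80 | 83.5 → **84** | 84.1 | 56.1 → 57 |
| AIS TXA-control, transfused | 531 | 1,318,745 | 55 | 54.6 → 55 | 55.0 | 36.7 → 37 |
| AIS EACA-control, units | 1.0 | 2.90 | 34 | 33.9 → 34 | 34.1 | 22.8 → 23 |
| NMS TXA-control, blood loss | 1282 | 1,968,781 | 14 | 13.99 → 14 | 14.1 | 9.4 → 10 |
| NMS TXA-EACA, blood loss | 859 | 1,255,124 | 30 | 19.9 → **20** | 20.0 | 13.4 → 14 |
| NMS TXA-control, transfused | 583 | 804,690 | 34 | 27.7 → **28** | 27.9 | 18.6 → 19 |

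Four rows match exactly at 0.01 with 80%. To the nearest whole number, 0.0167 with 85% fits the same four, so the setting is not unique. The same three rows fail under both.

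**Step 2: a check that needs no assumed alpha.** If the rows share one alpha and power, K = N × d² / (s₁² + s₂²) must be constant apart from rounding of N.

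- AIS: 11.80, 11.19, 11.76, 11.72.
- NMS: 11.69, 17.64, 14.36.

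Allow N to be rounded either way. The 80 row then gives at most 11.26 (N = 80.5), while the 58 row gives at least 11.59 (N = 57). The NMS rows of 30 and 34 give at least 17.05 and 13.94, while the NMS row of 14 gives at most 12.10. Reading every figure as a two-arm total halves every K alike, so the unit does not reconcile them. It would also leave the AIS figures with only about 64-66% power at two-sided 0.05.

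**Step 3: power at the planned arm sizes** (Welch t test, table inputs):

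| Row | Per arm | α 0.05 | α 0.0167 | α 0.01 |
|---|---|---|---|---|
| AIS TXA-control, blood loss | 50 | 88.4% | 77.1% | 70.9% |
| **AIS TXA-EACA, blood loss** | 50 | **74.2%** | **57.9%** | **50.4%** |
| AIS TXA-control, transfused | 50 | 89.9% | 79.6% | 73.8% |
| AIS EACA-control, units | 50 | 98.4% | 95.5% | 93.4% |
| NMS TXA-control, blood loss | 30 | 99.8% | 99.3% | 98.7% |
| NMS TXA-EACA, blood loss | 30 | 98.5% | 95.5% | 93.3% |
| NMS TXA-control, transfused | 30 | 93.8% | 85.8% | 80.8% |

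**Step 4: detectable TXA-EACA difference at 80% power**, (z₁₋α/₂ + z₁₋β) × √((s₁² + s₂²)/n), table SDs:

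- AIS, √(229,025/50) = 67.7: 2.802 × 67.7 ≈ 190 mL at 0.05; 3.417 × 67.7 ≈ 231 mL at 0.01. The table assumes 179 mL.
- NMS, √(1,255,124/30) = 204.5: 573 mL at 0.05; 699 mL at 0.01. The table assumes 859 mL.

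**Step 5: direction.** Both TXA-EACA rows have the lower loss on EACA (893 against 1072 mL; 1117 against 1976 mL). The hypothesis is that TXA does better.

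**The case against.** The strongest reply is that the strict alpha is inferred. At two-sided 0.05 and 80% power the three AIS placebo rows need 39, 37 and 23 per arm, all below 50, and the one remaining gap is 57 against 50. The protocol expects smaller variation at a single institution and will also calculate blood loss in a way meant to reduce variance. It also plans a collective analysis, up to 50 + 30 + 50 = 130 per arm, and a second power analysis after 60 patients.

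Much of this stands. On the placebo rows it is right. For AIS TXA-EACA, SDs smaller by the factor 179/190 = 0.94, about 6%, would restore 80% power at 0.05 (normal approximation). At 0.01 the factor is 179/231 = 0.77, and one of the SDs is already only 220 mL. The pooled analysis does not answer the separate AIS question, and no rule is given for what follows the re-check.

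Several stronger inferences are not supported:

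- That NMS is underpowered because 34 exceeds 30. The 34 is itself too high; its inputs give 28, and 30 per arm has 81-99% power even at 0.01.
- That the text claims an AD power calculation. It attributes the numbers to a literature review and points to tables captioned for AIS and NMS only.
- That the reversed direction makes the sample sizes wrong. A two-sided size depends only on the absolute difference.
- That a null result will be presented as equivalence. The article plans no such claim.

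The full protocol may state alpha and power. That would not make the printed rows agree with each other.

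**Conclusion.** The point holds in this limited form. The AIS arm size is not reconciled with the table said to support it, and three of the seven sample sizes (80, 30, 34 in NMS) are inconsistent with the other four under the standard formula, whatever common alpha, power or unit is assumed. The AIS TXA-EACA figure is slightly too low (80 against 84 at the inferred setting); the two NMS figures are too high and cost no power.

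The shortfall that remains at each two-sided alpha examined is AIS TXA-EACA, with 74% power at 0.05, 58% at 0.0167 and 50% at 0.01. Two AIS placebo rows drop below 80% only at the stricter alphas. The sized TXA-EACA effect is not the hypothesized one, which weakens the rationale but not the arithmetic.

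These results take the table means and SDs at face value, assume 1:1 allocation with full arms and no losses, and treat alpha, power and the per-arm unit as inferred.

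**What to change.** Correct the text and tables:

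- Restate Tables 2 and 3 under one stated two-sided alpha and one power, with the unit given as per arm.
- Recompute the AIS TXA-EACA row (80) and the NMS TXA-EACA and transfusion rows (30 and 34).
- State the power delivered at 50 per AIS arm and 30 per NMS arm, and say plainly that AIS TXA-EACA is below 80%.
- Give the TXA-EACA detectable difference with its alpha: at 80% power and the table SDs, about 190 mL (AIS) and 573 mL (NMS) at 0.05, or 231 and 699 mL at 0.01.
- Note that the TXA-EACA rows rest on cross-study differences running against the hypothesis.
- State that the tables do not support the AD arm size.

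No extra patients are needed and the design does not change. The cost is a less favorable stated power for the AIS head-to-head comparison.

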### Study Design

The study is designed as a prospective, randomized, double-blinded control trial. The patient, researcher, surgeon, and anesthesiologist will all be blinded to the patient's treatment. Patients will either receive TXA, EACA, or normal saline. The study will determine and compare differences in blood loss intra-operatively and estimate blood loss postoperatively through monitoring of subfascial Hemovac drain outputs at the incision site between the three groups. Postoperatively, laboratory values, drain outputs, and clinical outcomes will be carefully followed.

The primary goal of this study is to compare the efficacy of TXA to EACA to placebo in patients undergoing corrective spinal surgery for adolescent idiopathic scoliosis (AIS), neuromuscular scoliosis (NMS), and with adult deformity (AD). Outcome measures will include intra-operative and perioperative blood loss, transfusion rates, complete blood counts, and coagulation profiles, as well as postoperative wound drainage, complications, and length of stay.

### Standardized treatment protocol

The infusion is started 15 minutes prior to incision. The infusion is given in two parts. First a loading dose is given over 15 minutes at a volumetric rate of 20 ml/hour for a 50 kg patient. Following the initial loading dose, a maintenance dosage is given at one-tenth of the loading dose or 2 ml/hour for a 50 kg patient. This volumetric rate is adjusted accordingly for the patient's body weight. The volume infused remains constant regardless of whether the patient is receiving TXA, EACA, or saline. TXA is administered at 10 mg/kg hr for a loading dose followed by 1 mg/kg hr for a maintenance dose. In contrast, EACA is administered at 100 mg/kg hr for a loading dose, followed by 10 mg/kg hr for a maintenance dose. To adjust for this difference, the pharmacy is instructed to prepare the EACA at a tenfold higher concentration (250 mg/ml) than the TXA (25 mg/ml). The TXA and EACA treatments are both prepared in saline and both treatment preparations are visually indiscernible from saline alone. The loading and maintenance doses for TXA and EACA used in the protocol are in accordance with recent literature citing efficiency and safety at these dosages [7,8,10-14]. The literature also reports safely using TXA at a 100 mg/kg loading dose followed by a 10 mg/kg hr maintenance dose. However, improved efficacy at this higher dose of TXA has not been proven in a single orthopedic study. Since TXA is reported to be ten times more potent than EACA, delivering a dose of TXA that is ten times smaller than EACA is valid and well supported in the literature.

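### The loading dose is labelled as an hourly rate but runs for 15 minutes, so the load delivered is 2.5 mg/kg TXA or 25 mg/kg EACA, a quarter of the labelled figure, and no total is stated

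*Protocol article*

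**What the plan says.** All of the text at issue is in the protocol article, section Standardized treatment protocol.

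- Timing: "The infusion is started 15 minutes prior to incision".
- Load, as a pump setting: "First a loading dose is given over 15 minutes at a volumetric rate of 20 ml/hour for a 50 kg patient".
- Maintenance, as a pump setting: "a maintenance dosage is given at one-tenth of the loading dose or 2 ml/hour for a 50 kg patient". Rates are scaled to body weight, and the volume is the same in all three arms.
- TXA dose: "TXA is administered at 10 mg/kg hr for a loading dose followed by 1 mg/kg hr for a maintenance dose".
- EACA dose: "EACA is administered at 100 mg/kg hr for a loading dose, followed by 10 mg/kg hr for a maintenance dose".
- Concentrations: 25 mg/ml for TXA and 250 mg/ml for EACA.
- Support for the doses: they are said to be "in accordance with recent literature citing efficiency and safety at these dosages".
- A comparison regimen: "The literature also reports safely using TXA at a 100 mg/kg loading dose followed by a 10 mg/kg hr maintenance dose". The section then adds that "improved efficacy at this higher dose of TXA has not been proven in a single orthopedic study".

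The load is never given as a total, whether in mg/kg, mg or ml.

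**The concern.** A loading dose is normally understood as an amount. Here it is written in the unit of a rate, and the rate applies for only a quarter of an hour. A reader who carries away 10 and 100 as the loading figures will have four times what the pump settings deliver.

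The comparison regimen makes that misreading easier, because its load is an amount and only its maintenance is a rate. The trial's load and the comparison load therefore stand close together on different scales.

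Dose is the intervention in this trial, and the load is timed to be in by incision. If totals of 10 and 100 mg/kg were meant, the instruction as written delivers a smaller load than planned in both active arms. If 2.5 and 25 mg/kg were meant, the treatment is as planned, but its description invites readers to credit the trial with testing a load four times larger.

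**Working it through.** **Inputs**, all from Standardized treatment protocol: 50 kg reference patient; load 20 ml/hour for 15 minutes (0.25 h); maintenance 2 ml/hour; TXA 25 mg/ml; EACA 250 mg/ml; comparison TXA regimen 100 mg/kg, then 10 mg/kg hr.

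**Step 1: reproduce the stated rates.** Rate in mg/kg/h = (ml/h × mg/ml) / kg.

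| | Load | Maintenance |
|---|---|---|
| TXA | 20 × 25 / 50 = 10 | 2 × 25 / 50 = 1 |
| EACA | 20 × 250 / 50 = 100 | 2 × 250 / 50 = 10 |

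All four match the text. The one-tenth rule also holds, rate against rate: 2/20, 1/10 and 10/100.

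**Step 2: the load delivered.** Volume = 20 ml/h × 0.25 h = 5 ml.

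- TXA: 5 × 25 = 125 mg; 125 / 50 = 2.5 mg/kg.
- EACA: 5 × 250 = 1250 mg; 1250 / 50 = 25 mg/kg.

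Each is one quarter of the labelled figure (2.5/10 and 25/100). Because the pump rate scales with weight, the mg/kg result is the same at any weight.

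**Step 3: what totals of 10 and 100 mg/kg would need.**

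- TXA: 10 × 50 / 25 = 20 ml.
- EACA: 100 × 50 / 250 = 20 ml.
- Over 15 minutes: 20 / 0.25 = 80 ml/hour.
- At the stated 20 ml/hour: 20 / 20 = 1 hour, which does not fit the 15 minutes allowed.

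**Step 4: comparison regimen against the trial (TXA).**

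| | Maintenance | Load |
|---|---|---|
| Trial as written | 10 / 1 = 10-fold | 100 / 2.5 = 40-fold |
| Trial with a 10 mg/kg total load | 10 / 1 = 10-fold | 100 / 10 = 10-fold |

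The comparison scales evenly only if the trial's load is a 10 mg/kg total. It concerns TXA alone. A 100 mg/kg EACA load follows only through the tenfold TXA:EACA ratio, and 2.5 to 25 mg/kg satisfies that ratio equally well.

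**The case against.** The strongest reply is that the instruction is complete and unambiguous. Duration, pump rate, concentration and labelled rate all agree, so anyone following the text gives one definite dose, and 15 minutes at 20 ml/hour fixes the total whether or not it is written down. This stands: there is no contradiction among the stated figures, and the per-hour unit is not a stray slip, since the pump rate carries it too.

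Three stronger readings are tempting, and the document does not support them.

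- A reader might infer that the one-tenth rule is broken, because 2 ml is not a tenth of the 5 ml delivered. The section expresses the load as a rate, and rate against rate the rule is right.
- A reader might infer that 10/100 mg/kg was certainly intended. The section calls the comparison regimen only a higher dose, which is true against either 2.5 or 10 mg/kg. It does not say that the regimen is tenfold in both parts. A missing per-hour unit in that sentence could also explain the mismatch: if 100 mg/kg/h were run for 15 minutes (an assumption), the load would be 100 × 0.25 = 25 mg/kg, and 25 / 2.5 is again 10-fold.
- A reader might infer that the claim of agreement with the literature is false. The cited sources are not at hand, and nothing in the article shows the claim to be wrong for a 2.5/25 mg/kg load.

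It can also be said that an article condenses a fuller protocol, where a total may appear. That is possible. But this article gives minutes, ml/hour, mg/ml and mg/kg hr, so the point concerns how a detailed specification is labelled, not a detail left out.

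**Conclusion.** The point holds as a labelling fault in the intervention with a fourfold consequence. The figures presented as loading doses are 10 and 100, and the loads delivered are 2.5 mg/kg TXA and 25 mg/kg EACA. The arithmetic is exact and needs no assumption beyond the stated settings.

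Which load was intended cannot be settled from the document. The TXA comparison favours 10/100 mg/kg totals but does not establish them. Only under that intention would patients receive a smaller load than planned. The effect on total exposure cannot be sized, because the length of maintenance is not stated.

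The TXA:EACA dose ratio, the matched infusion volumes and the blinding are untouched. The comparison with placebo remains valid for the regimen actually given.

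**What to change.** 1. Confirm the intended load.
2. State it as a total in mg/kg and in ml for a 50 kg patient, and keep mg/kg/h for maintenance only.
3. Check the pharmacy order form and the pump settings against that total.
4. If 10/100 mg/kg was intended and no patient has been dosed, set the load at 80 ml/hour for 15 minutes (20 ml for 50 kg).
5. If 2.5/25 mg/kg was intended, or patients have already been dosed as written, keep the regimen, report it as a 2.5/25 mg/kg load, and check the statement of agreement with the literature against the cited sources on that basis.

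Rewording and checking the form and settings cost little. Changing the pump rate is cheap only before the first dose. The section Medication Supply and Randomization describes NMS and AD patients as a later addition to the study, so dosing may already have begun. A change at that stage would mix two loads within each active arm, and relabelling would be the cheaper route.
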